## **GLOSSARY OF ABBREVIATIONS**

|             |                                                                |
|-------------|----------------------------------------------------------------|
| AE          | Adverse event                                                  |
| ANOVA       | Analysis of variance                                           |
| ASR         | Annual safety report                                           |
| CA          | Competent authority                                            |
| CFR         | Code of Federal Regulations                                    |
| CI          | Confidence interval                                            |
| CRO         | Contract research organization                                 |
| eCRF        | Electronic case report form                                    |
| EDC         | Electronic data capture                                        |
| Eform       | Electronic form                                                |
| ESF         | Eligibility screening form                                     |
| FDA         | Food and Drug Administration                                   |
| GCP         | Good Clinical Practice                                         |
| ICH         | International Conference on Harmonization                      |
| IEC         | Independent Ethics Committee                                   |
| IRB         | Institutional Review Board                                     |
| LPLV / LSLV | Last patient last visit / last subject last visit              |
| MedDRA      | Medical Dictionary for Regulatory Activities Terminology       |
| mRNA        | messenger Ribonucleic Acid                                     |
| MOS         | Margin of safety                                               |
| SAE         | Serious adverse event.                                         |
| SI          | Système international d'unités (International system of units) |

## **GLOSSARY OF ABBREVIATIONS**

|       |                                               |
|-------|-----------------------------------------------|
| SoATs | Schedule of Assessment Tables                 |
| SMT   | Study management team                         |
| SUSAR | Suspected Unexpected Serious Adverse Reaction |
| TBD   | To be determined                              |
| USAN  | United States Adopted Name                    |
| HFMS  | Hammersmith Functional Motor Scale            |
| SMA   | Spinal Muscular Atrophy                       |
| SMN   | Survival motor neuron (gene or protein)       |

## **PART I: STUDY DESIGN AND CONDUCT**

### **1. BACKGROUND AND RATIONALE**

Spinal Muscular Atrophy (SMA) is a common inherited pediatric neuromuscular disorder. There currently is no cure and there are no therapeutics approved to slow progression of the disease. SMA is characterized by a loss of alpha motor neurons in the spinal cord, severe atrophy of proximal muscles and progressive debility and disability due to respiratory, gastrointestinal and functional complications of the disease. The disease is caused by a lack of the survival motor neuron (SMN) protein, which is coded by the SMN1 gene. Most SMA patients have a deletion of the SMN1 gene, but a small minority of patients have smaller point mutations in the SMN1 gene. Humans have a copy of a nearly identical gene, SMN2, which can compensate to some degree for the loss of SMN1 in SMA patients.

While several new therapies for SMA are poised to enter the clinic, there are a number of challenges to executing SMA trials that must be addressed. The putative target tissue for SMA treatment is the spinal cord, a tissue that cannot be sampled directly to evaluate drug effects. Thus it is important to develop meaningful measurements from accessible tissues like blood that relate to changes in the spinal cord. Also, SMA is a disease that presents in a heterogeneous manner with a spectrum of motor function (from not being able to sit up to not being able to walk) and variability in disease onset (from birth to the third decade of life). The variability of SMA phenotypes requires careful consideration about which patients are best to enroll in each specific drug trial. Finally, although SMA is a relatively common orphan disease, recruitment of patients for the number of candidate therapies is expected to become rate-limiting for the development of therapeutics.

Several of the challenges described above can be met by developing 'biomarkers' that can help predict responses to drugs in SMA patients in simple blood specimens. A biomarker is a characteristic that is objectively measured and evaluated, and is an indicator of a biologic process. The potential advantages for developing biomarkers for SMA are many and largely can be applied to any new drugs that are tested, and the uses are listed below:

- May allow replacement of a distal endpoint with a proximal endpoint, potentially shortening the development time of new therapeutic modalities
- Measures in blood may be done more frequently and easily than costly and complex functional tests
- May have greater precision
- May increase the measured dynamic range of a disease process or treatment effect compared to clinical metrics
- May provide a rationale for the selection of a patient population more likely to respond positively to drugs
- May result in reduced sample size requirements for clinical studies
- May lead to expedited decisions concerning the validity of therapeutic interventions

Thus, the development of SMA biomarkers will have important implications in therapeutics development timelines and more efficiently allocate patient resources into studies with the greatest probability of success. **OBJECTIVES OF THE STUDY**

## **2.1 PRIMARY OBJECTIVE**

- To refine and validate mRNA assays for SMN1 and SMN2 detection in blood from SMA patients.
- To measure SMN protein in whole blood and in isolated lymphocytes in SMA patients.
- To establish correlations between mRNA and protein levels in blood and SMN2 copy number in SMA patients
- To validate protocols for sample collection, SMN mRNA and protein quantitation in SMA patients

## **2.2 SECONDARY OBJECTIVES**

To collect blood samples that could be used to continue validation of new mRNA or protein biomarkers for SMA. Any new SMA biomarker could ultimately be used as a tool in clinical trials to determine if patient functional status is changing in response to drug treatment.

## **3. STUDY DESIGN**

### **3.1 OVERVIEW OF STUDY DESIGN**

This study will be a single visit study enrolling up to 40 patients. The study will enroll patients that are self-identified SMA patients.

This is a multi center study to be conducted in the USA. An additional site(s) may be included for back-up purposes and may be activated if needed. *Administrative and Contact Information and List of Investigators* are provided separately.

#### **3.1.1 End of Study Definition**

The end of the trial is defined as the date of the last visit of the last patient undergoing the trial.

## **4. STUDY POPULATION**

### **4.1 TARGET POPULATION**

Three groups of SMA patients may be enrolled according to the classifications below:

- Patients with type I SMA (max of 10)
- Patients with type II SMA (minimum of 5 and maximum of 15)
- Patients with type III SMA (minimum of 5 and maximum of 15)

#### **4.1.1      Recruitment Procedures**

The Principal Investigator (or designee) and the study coordinator will have responsibility for patient recruitment in conjunction with the local chapter of the Families of SMA who will pre-identify patients within their network.

#### **4.2              INCLUSION CRITERIA**

A patient may be included if the answer to all of the following statements is 'yes':

1. Self-identified as 5q-autosomal recessive SMA type I, II, or III as judged by their neurologist upon diagnosis.
2. Ability and willingness to provide blood samples.
3. Willingness (by the patient or patient's parents or legal guardian) to complete to their best ability a questionnaire which requests specific clinical and genetic information.
4. Able to participate and willing to give written informed consent or assent. Informed consent will be obtained from the patient, or the patient's parent or legal guardian.

#### **4.3              EXCLUSION CRITERIA**

A patient will be excluded if the answer to any of the following statements is 'yes':

1. Any known genetic condition other than Spinal Muscular Atrophy, unless it is not interfering with the purpose of this study based on the Sponsor's judgment.
2. Participation in a clinical trial (except observational studies) within the previous 14 days.
3. Donation of blood or significant blood loss within three months prior to screening.
4. Concomitant disease or condition that could interfere with, or treatment of which might interfere with, the conduct of the study, or that would, in the opinion of the investigator, pose an unacceptable risk to the patient in this study.

#### **4.4              CRITERIA FOR PREMATURE WITHDRAWAL**

Patients have the right to withdraw from the study at any time for any reason. In the event that a patient decides to prematurely discontinue from the study, he/she should be asked if he/she can still be contacted for further information. The outcome of that discussion should be documented in both the medical records and in the eCRF.

When applicable, patients should be informed of circumstances under which their participation may be terminated by the investigator without the patient's consent. The investigator may withdraw patients from the study in the event of intercurrent illness, adverse events, lack of compliance with the study and/or study procedures (e.g., study visits) or any other reason where the investigator feels it is in the best interest of the

patient to be terminated from the study. Reasons for withdrawal must be documented and explained to the patient. It is understood by all concerned that an excessive rate of withdrawals can render the study uninterpretable; therefore, unnecessary withdrawal of patients should be avoided. Should a patient decide to withdraw, all efforts should be made to complete and report the observations as thoroughly as possible.

If the reason for removal of a patient from the study is an AE related to study procedures, the principal specific event must be recorded on the eCRF. The patient should be followed until the AE is resolved, if possible.

#### **4.5 CONCOMITANT MEDICATION AND TREATMENT/SPECIAL DIETARY REQUIREMENTS**

All medications (prescription and over-the-counter [OTC]) taken within 30 days before the screening / study visit will be recorded on the appropriate eCRF.

#### **5. SCHEDULE OF ASSESSMENTS AND PROCEDURES**

At the time of enrollment, the research staff will use the patient questionnaire to obtain self-declared clinical history and other information:

- Gender
- Age
- Race
- SMA Type (I or II or III)
- Age at onset
- SMN2 copy number (if known by the patient)
- Hammersmith Functional Motor Scale (HFMS) or equivalent (if known)
- If the patient has taken any potentially SMN-enhancing drugs in the past 7 days, eg. valproic acid, phenylbutyrate, hydroxyurea, carnitine, riluzole, creatine, oral albuterol
- Patient's current level of function (sitting without support, rolling, crawling, standing, walking )
- Highest motor function achieved ( sitting without support, rolling, crawling, standing, walking)

## **5.1 SCREENING AND ENROLLMENT**

### **5.1.1 Screening Examination and Eligibility Screening Form**

All patients or their parent/legal guardian must sign and date the most current IRB/IEC-approved written informed consent before any study specific assessments or procedures are performed. Children older than seven years will be asked to sign an assent. An original signed consent form will be retained by the investigator and the patient will receive a copy to take home.

An Eligibility Screening Form (ESF) documenting the investigator's assessment of each screened patient with regard to the protocol's inclusion and exclusion criteria is to be completed and signed by the investigator (or designee).

A screen failure log must be maintained by the investigator.

Ethnicity of patients will be recorded since this information might be important to evaluate a potential impact of ethnic factors on biomarkers (see also ICH Guideline E5(R1)).

### **5.1.2 Enrollment procedure**

Patients cannot commence enrollment procedures until all entry criteria have been fulfilled.

Under no circumstances will patients who enroll in this study and have provided a blood sample as specified, be permitted to re-enroll in the study. A patient Enrollment and Identification Code List must be maintained by the investigator.

## **5.2 STUDY PROCEDURES/ASSESSMENTS**

### **5.2.1 Study Procedures**

Signed and dated IRB-approved informed consent or assent must be obtained from the patient, or the patient's parent or guardian, before any study-specific screening procedures are performed. The possible benefits and complications of participation will be explained in detail. Every effort will be made to ensure that the patient and parent/guardian fully comprehend the nature of the study and the details of his or her participation. A copy of the consent form will be provided to the parent/guardian and patient. The informed consent process must be documented in the patient's study record.

After the inclusion and exclusion criteria have been assessed and a patient was judged to be eligible for the study, sample collection for the study will take place on the same day and during the same visit.

### **Blood Sample Collection**

The following mandatory samples will be collected in order of priority:

- **Blood for RNA Expression Profiling**  
Blood (approximately 2.5 mL collected in PAXgene vacutainers) for RNA isolation will be obtained from every patient.
- **Whole blood for protein analysis**  
One blood (approximately 3 mL) sample for SMN protein analysis will be collected from every patient. Collected samples may be used for exploratory studies in order to correlate SMN protein with other biomarkers of SMA.
- **Whole Blood for DNA Analysis**  
A whole Blood sample of approximately 3 mL will be taken from every patient for DNA extraction and analysis of genetic information. The genetic information collected will be related to SMN1 and SMN2 and may include additional genes in the disease pathway of SMA.
- **Plasma for biomarker analysis**  
Blood (one approximately 6.0 mL sample in EDTA) for plasma isolation will be obtained. These samples will be used for biomarker assays which may include IGF and IGF binding proteins, the SMA Multi-analyte panel or other candidate SMA biomarkers.
- **Serum for biomarker analysis**  
Blood (one approximately 6.0 mL sample in a plain tube without EDTA) for serum isolation will be obtained. These samples will be used for biomarker assays which may include IGF and IGF binding proteins, the SMA Multi-analyte panel or other candidate SMA biomarkers.

For sampling procedures, storage conditions and shipment instructions see study Sample Handling and Logistics Manual.

### **Total Blood Loss**

A total of up to 21 mL of blood will be drawn from each patient. In case patients are considered too fragile or below 15kg of body weight, only samples for RNA Expression profiling and protein analysis will be collected.

After collection of the blood samples and completion of the questionnaires, patients will get dismissed and their participation in the study is considered complete. No specific follow-up assessment will take place.

**Table 1 Number of Samples and Approximate Amount of Blood to be collected from Each Patient**

| Test                               | Day 1 | Total No. of Samples | Approx. No. of mL per Sample | Sub-Total mL of Blood |
|------------------------------------|-------|----------------------|------------------------------|-----------------------|
| Blood for RNA expression profiling | 1     | 1                    | 2.5                          | 2.5                   |
| Whole blood for protein analysis   | 1     | 1                    | 3                            | 3                     |
| Whole blood for DNA analysis       | 1     | 1                    | 3                            | 3                     |
| Plasma for biomarker analysis      | 1     | 1                    | 6                            | 6                     |
| Serum for biomarker analysis       | 1     | 1                    | 6                            | 6                     |
| Approximate Total Blood Volume     |       |                      |                              | 20.5                  |

#### **5.2.1.1 Biomarker Assessments**

All biomarkers which will be explored in this study are related to SMA. Measurements of biomarkers will comprise mRNAs of SMN1 and SMN2 and SMN protein. Measurements include also additional mRNAs or proteins to be used as standards for quantification. Biomarker assessment may also include candidate biomarkers for SMA related to the clinical phenotype.

Genotyping will be performed on each patient including but not limited to determining the copy number of SMN2 since the severity of SMA is modulated by the number of copies of SMN2 which in turn modulates the levels of SMN protein. The genetic information collected will be related to SMN1 and SMN2 and may include additional genes in the disease pathway of SMA.

## **6. SAFETY INSTRUCTIONS AND GUIDANCE**

Safety assessments will consist of monitoring and recording adverse events, including serious adverse events and non-serious adverse events of special interest.

Certain types of events require immediate reporting to the Sponsor, as outlined in Section 6.3.

## **6.1 ADVERSE EVENTS**

### **6.1.1 Adverse Events**

According to the ICH guideline, as patients will not receive an investigational drug in the study, only study procedure-related adverse events and events of interest will be reported.

Study procedure-related adverse events are events which the investigator regards to be clinically relevant and related directly to the procedures of the study e.g. blood sampling.

Events of interest include events leading to death, hospitalizations, any procedure complications or disease progression that appears more rapid than expected.

All AEs encountered during the study and for up to 28 days after the study visit which are clinically relevant and related directly to the procedures within this protocol will be reported on the AE form of the eCRF. At the study completion/early termination visit, the investigator should instruct each patient to report to the investigator any subsequent adverse events that the patient's personal physician believes could be related to study procedures.

The investigator should notify the Sponsor of any death, serious adverse event, or other adverse event of concern occurring at any time after a patient has discontinued study participation if the event is believed to be related to study procedures.

For Good Clinical Practice, an adverse event is any untoward medical occurrence in a clinical investigation subject administered a pharmaceutical product, regardless of causal attribution. An adverse event can therefore be any of the following:

- Any unfavorable and unintended sign (including an abnormal laboratory finding), symptom, or disease temporally associated with the use of a medicinal product, whether or not considered related to the medicinal product.
- Any new disease or exacerbation of an existing disease (a worsening in the character, frequency, or severity of a known condition). Recurrence of an intermittent medical condition (e.g., headache) not present at baseline.
- Any deterioration in a laboratory value or other clinical test (e.g., ECG, X-ray) that is associated with symptoms or leads to a change in study treatment or concomitant treatment or discontinuation from study drug.
- Adverse events that are related to a protocol-mandated intervention, including those that occur prior to assignment of study treatment (e.g., invasive screening procedures such as biopsies).

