### **6.2.3      Assessment of Causality of Adverse Events**

Investigators should use their knowledge of the patient, the circumstances surrounding the event, and an evaluation of any potential alternative causes to determine whether or not an adverse event is considered to be related to the procedure, indicating "yes" or "no" accordingly. The following guidance should be taken into consideration:

- Temporal relationship of event onset to the study procedure
- Known association of the event with the study procedures
- Known association of the event with the disease under study
- Presence of risk factors in the patient or use of concomitant medications known to increase the occurrence of the event
- Presence of non-treatment-related factors that are known to be associated with the occurrence of the event

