### **6.3 IMMEDIATE REPORTING REQUIREMENTS FROM INVESTIGATOR TO SPONSOR**

Certain events require immediate reporting to allow the Sponsor to take appropriate measures to address potential new risks in a clinical trial. The investigator must report such events to the Sponsor immediately; under no circumstances should reporting take place more than 24 hours after the investigator learns of the event. The following is a list of events that the investigator must report to the Sponsor within 24 hours after learning of the event, regardless of relationship to study procedure:

- Serious adverse events
- Non-serious adverse events of special interest
- Pregnancies

The investigator must report new significant follow-up information for these events to the Sponsor immediately (i.e., no more than 24 hours after becoming aware of the information). New significant information includes the following:

- New signs or symptoms or a change in the diagnosis
- Significant new diagnostic test results
- Change in causality based on new information
- Change in the event’s outcome, including recovery
- Additional narrative information on the clinical course of the event

Investigators must also comply with local requirements for reporting serious adverse events to the local health authority and IRB/EC.

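### The only visible post-visit reporting instruction depends on a personal physician's view of relatedness, so events the protocol wants regardless of cause may not reach the investigator

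*Protocol*

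**What the plan says.** Section 3.1: "This study will be a single visit study enrolling up to 40 patients". The subsection on total blood loss in 5.2.1 adds that participation counts as complete once samples and questionnaires are done, and that "No specific follow-up assessment will take place".

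Section 6.1.1 sets the reporting period: "All AEs encountered during the study and for up to 28 days after the study visit". That sentence goes on to confine eCRF reporting to clinically relevant events directly related to the protocol's procedures. The same section also names a wider group: "Events of interest include events leading to death, hospitalizations, any procedure complications or disease progression that appears more rapid than expected".

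For the time after the visit, 6.1.1 has the investigator instruct each patient to report to the site later adverse events that the patient's "personal physician believes could be related to study procedures".

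The relatedness judgement is assigned elsewhere. Section 6.2.3 begins: "Investigators should use their knowledge of the patient, the circumstances surrounding the event, and an evaluation of any potential alternative causes", and asks for a yes or no answer. Section 6.1.1 likewise defines procedure-related events by what the investigator considers related.

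Section 6.3 lists serious adverse events, non-serious events of special interest and pregnancies for 24-hour reporting to the sponsor, "regardless of relationship to study procedure". Section 6.2.4.1 asks for every death in the reporting period, again whatever its cause.

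**The concern.** In a trial with several visits, a sentence like the one in 6.1.1 covers the tail after active collection has ended. Here the completion visit is the blood draw itself, so the sentence has to serve for the entire period after the procedure. It asks for events that have first passed through a physician who has no other role in the protocol and need not know what was sampled or when.

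Completeness of safety capture is at stake. The causality assessment in 6.2.3, the 24-hour duty in 6.3 and the follow-up in 6.4.1 all start once the investigator knows of an event, and the screen sits before all three. If few post-visit events are recorded, a reader of the safety listings could not tell whether few occurred or few were passed on.

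**Working it through.** The protocol gives no figure to reproduce, so the check is a comparison of its own rules.

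**Step 1: count the routes by which a post-visit event can reach the site.**
- Visits: 1 (section 3.1).
- Scheduled contacts in the 28 days after the visit: 0 (5.2.1, total blood loss).
- Prompted questioning: section 6.2.1 ties it to patient evaluations, and there is one. Its sample questions ask about the time since a previous visit, which no patient in this study has.
- Patient reporting instructions visible in the protocol: 1, the sentence in 6.1.1.

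That sentence therefore carries the whole window.

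**Step 2: compare what the protocol wants with what the sentence asks for.**

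| Event after the visit | Where it is wanted | Limited to related events? | When the 6.1.1 instruction covers it |
|---|---|---|---|
| Death | 6.2.4.1 | No | A physician suspects the procedure |
| Serious adverse event | 6.3 | No | A physician suspects the procedure |
| Non-serious event of special interest | 6.3 | No | A physician suspects the procedure |
| Pregnancy | 6.3 | No | Hardly ever fits the wording |
| Hospitalization, faster-than-expected progression | 6.1.1, events of interest | Not stated as limited | A physician suspects the procedure |
| Procedure complication | 6.1.1 | Related by nature | A physician sees it and suspects the procedure |

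In the first five rows the protocol does not make relatedness a condition, but the instruction does. In the last row the event is within scope, yet it falls outside the instruction if it is never shown to a physician.

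**Step 3: check who judges relatedness.** Sections 6.1.1 and 6.2.3 both name the investigator. The personal physician does not replace that assessment, but does influence which events arrive for it.

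**Step 4: check the neighbouring notification rule.** Section 6.1.1 also has the investigator notify the sponsor of deaths, serious events and other events of concern arising after a patient has discontinued participation, if they are believed to be related. Section 5.2.1 treats participation as complete at dismissal. If completion counts as discontinuation, an unrelated death within the 28 days falls under this restricted rule and under the unrestricted one in 6.2.4.1. If discontinuation means early withdrawal alone, the overlap is much smaller. The text does not say which is meant.

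**The case against.** The strongest case against the point is that the sentence is less restrictive than it looks.

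- *A reader might infer that patients are told to report nothing else.* The sentence does not limit reporting in that way and forbids no other report. This part of the objection stands. What remains is that no other instruction is visible.
- *A reader might infer that an outside physician decides causality.* The text does not support this. The threshold is that the event could be related, and the formal assessment stays with the investigator.
- *A reader might infer that unrelated events cannot reach the site, or that 6.3 would be breached.* Neither follows. Investigators may learn of events by other means, and the 24-hour duty runs from when they learn of them. The supportable wording is that such events may not reach the investigator.
- *The consent pages are not part of the text reviewed.* What patients are told in writing about contacting the site cannot be seen, so the point is limited to the visible protocol.
- *The stakes are low.* There is no study drug, one draw of about 20.5 mL (Table 1), and descriptive adverse-event output (7.1.1). No primary objective depends on post-visit events. This is fair, and it limits the weight of the point.

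None of this removes the mismatch. The instruction, followed as written, asks patients for less than 6.1.1, 6.2.4.1 and 6.3 require.

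**Conclusion.** The point holds as a mismatch of scope in safety capture. The one visible instruction for the period after the visit is conditioned on a personal physician's view of relatedness, while the protocol wants several categories of event without that condition. It applies to all of up to 40 patients and to the full 28 days.

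The size of any loss cannot be estimated. The documents give no rate for how often patients would consult a physician, how often that physician would suspect the procedure, or how often patients would report unprompted, so any capture percentage would be guesswork. It is also tempting to say that the loss would be greatest in the more severely affected patients. Section 7 does call Type I patients particularly fragile, but nothing in the protocol shows differential reporting by SMA type.

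Two assumptions are needed: that patients act broadly on the instruction as worded, and that the 28-day window in 6.1.1 also frames the events in 6.3. Section 6.2.4.1 makes that link expressly for deaths, whereas 6.3 gives no window of its own. The consequence is confined to the completeness of safety reporting. The biomarker objectives and the number of patients are unaffected. The sentence should be corrected because the change is small and removes a real inconsistency.

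**What to change.** Reword the 6.1.1 sentence along these lines: at dismissal, the investigator asks the patient, parent or guardian to report directly to the site, for up to 28 days after the visit, any possible complication of the sampling, any death, hospitalization or other serious event, any other event of interest or of special interest, and any pregnancy, whether or not a physician thinks it related. The investigator then assesses relatedness under 6.2.3. The list should stay within the categories the protocol already requires. A request for every new or worsened health problem would go beyond that scope in a progressive disease.

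In the same revision, reconcile the 6.1.1 sentence on notification after discontinuation with 6.2.4.1 and 6.3. State whether a patient who has completed the visit counts as having discontinued. Check that whatever patients are given in writing carries the same instruction.

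The cost is a short text change and a few more unrelated reports for the investigator to triage. No visit, procedure or staff is added.
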